# Comparing cognitive behavioral therapy and social prescribing in patients with loneliness on long-term opioid therapy to reduce opioid misuse: protocol for a randomized controlled trial

**DOI:** 10.1186/s13722-024-00498-y

**Published:** 2024-09-11

**Keywords:** Loneliness, Opioid misuse, Opioid-related disorders, Opioid analgesics, Psychosocial interventions

## Abstract

**Background:**

Patients with chronic pain on opioids frequently experience loneliness, which is associated with poorer health outcomes and higher risk for opioid misuse and opioid use disorder. Given that almost half of opioids are prescribed in primary care, a critical need exists for the development and testing of interventions to reduce loneliness in primary care patients at risk for opioid misuse. Cognitive behavioral therapy and social prescribing have been shown to be efficacious in reducing loneliness and improving outcomes in other populations but have not been tested in patients at risk for substance use disorder. The overall objective of our study is to reduce opioid misuse and opioid use disorder by addressing loneliness in patients on long-term opioid therapy in real-world primary care settings.

**Methods:**

We will conduct a 3-arm pragmatic, randomized controlled trial to compare the effectiveness of two group-based, telehealth-delivered interventions with treatment as usual: (1) cognitive behavioral therapy to address maladaptive thought patterns and behaviors around social connection and (2) a social prescribing intervention to connect participants with social opportunities and develop supportive social networks. Our primary outcome is loneliness as measured by the UCLA Loneliness Scale and our dependent secondary outcome is opioid misuse as measured by the Common Opioid Misuse Measure. We will recruit 102 patients on long-term opioid therapy who screen positive for loneliness from 2 health care systems in Washington State. Implementation outcomes will be assessed using the RE-AIM framework.

**Discussion:**

Our study is innovative because we are targeting loneliness, an under-addressed but critical social risk factor that may prevent opioid misuse and use disorder in the setting where most patients are receiving their opioid prescriptions for chronic pain. If successful, the project will have a positive impact in reducing loneliness, reducing opioid misuse, improving function and preventing substance use disorder.

**Trial Registration:**

NCT06285032, issue date: February 28, 2024, original.

## Background

Individuals on long-term opioid therapy frequently experience loneliness, which is associated with poorer health outcomes and higher risks for opioid misuse and opioid use disorder [1]. Loneliness, which refers to the perceived lack of connections to others and the feeling of not belonging [2] has increased substantially during the COVID-19 pandemic to greater than half of U.S. adults [3–6]. Loneliness as a mediating factor leading to substance use disorder is becoming increasingly relevant as rates of drug overdose, substance use disorder and opioid misuse continue to rise substantially, exacerbated by the COVID-19 pandemic and the resultant social and physical isolation [7–11]. Even before the pandemic, a brief decline in drug overdose deaths had reversed despite substantial efforts to reduce opioid prescribing in the United States [12]. Meanwhile, initial decreases in opioid prescribing have plateaued during the COVID-19 pandemic as barriers to non-pharmacologic modalities of treating chronic pain increased [13, 14] leading to worsening care for patients with chronic pain [15]. Many experts have hypothesized that the social distancing requirements initially put in place during the pandemic resulted in decreased social connection and increased loneliness resulting in increased risk for opioid misuse and overdose [16].

A 2023 U.S. Surgeon General Advisory highlighted the association of loneliness with poor health outcomes and proposed a national strategy for addressing loneliness [17]. This strategy includes 6 pillars, of which one concerns mobilization of the health care sector. This is relevant because individuals experiencing loneliness have greater healthcare utilization in both outpatient [18, 19] and acute care [20, 21] settings.

Primary care could play an important frontline role in reducing loneliness in those on long-term opioid therapy to potentially reduce risk for opioid misuse and opioid use disorder. As the most common and often first setting where individuals seek care [22], primary care treats over half of the patients with chronic pain and prescribes almost 50% of opioids nationwide [23, 24]. Our preliminary work [25, 26] and other studies [27] have suggested that at least 20% of primary care patients reported loneliness that impact their chronic conditions and functioning. As such, a primary care based intervention will have the highest likelihood of reaching the most patients to address loneliness and prevent opioid misuse and overdose. In addition, primary care focuses on prevention [28] and growing literature suggests that prevention of addiction (and the recognition of preaddiction as an important precursor to substance use disorders) is important and undervalued [29, 30].

The overall objective of our study is to adapt and test two evidence-based loneliness interventions, cognitive behavioral therapy (CBT) and social prescribing, with the goal of reducing opioid misuse and opioid use disorder in primary care patients with chronic pain. These two interventions have shown efficacy in reducing loneliness and improving health outcomes primarily in older adults [31, 32] but have yet to be tested for patients on long-term opioid therapy.

Our study’s specific aims are:

To determine the effectiveness of two group based, telehealth-delivered loneliness interventions (CBT and social prescribing) relative to usual care in reducing loneliness (primary outcome) and opioid misuse (secondary outcome) in a 3-arm randomized controlled trial.

### Hypothesis

We hypothesize that both CBT and social prescribing will be superior to usual care in reducing loneliness and that reductions in loneliness will then lead to reductions in opioid misuse. We hypothesize that CBT and social prescribing will be noninferior.

2)To assess implementation outcomes using the RE-AIM framework from a 3-arm randomized controlled trial testing the CBT and social prescribing interventions in primary care practices.

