### Power analysis

We plan to recruit 102 patients on long-term opioid therapy based on a sample size calculation allowing us to detect 6-point changes or more in the UCLA loneliness scale (Version 3). The 6-point change was determined by the mean loneliness score change from a previously published meta-analyses of psychological interventions for loneliness [31]. For the sample size calculation, we also assumed a significance level of 0.05, a desired power of 0.80, and a standard deviation of 8.0 (from weighted average from the original validation of the UCLA loneliness scale). Based on this, we will require 28 patients per arm. Assuming an 80% retention rate, we plan to recruit 34 patients per arm (or 102 patients total).

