### Quantitative analysis

The analysis population will include all randomized patients. Patients will be analyzed according to their assigned intervention group, regardless of what treatment they receive (intent to treat analysis). Descriptive statistics (mean and standard deviation) will be used to summarize the distribution of the primary outcome (loneliness), and secondary outcomes (opioid misuse, depression, anxiety, functionality and opioid dose) at baseline, immediately following the intervention and 3 months following the intervention. Linear mixed models will be used to test the association between the intervention arm and the change in the primary outcome and secondary outcomes across the study period. Since we expect that the effect from the intervention takes places immediately after implementation, we will include the intervention arm (control arm as the reference), an indicator for the post-treatment time points (immediately following the intervention and 3 months after) as well as their interaction as independent variables. Intervention assignment will be modeled as a fixed effect, and individual participants will be modeled as a random effect. Each model will contain a random intercept to account for the subject-specific correlation in outcome. In a secondary analysis, we will add a contrast variable to test the maintenance of outcomes between the second and third time points.

Subgroup analyses, which will be exploratory in nature, will be performed using the same modeling technique to assess the heterogeneity of treatment effects across subgroups of patients defined by age (grouped by tertiles), gender (male, female and nonbinary), rurality (rural urban continuum codes), initial opioid MME (calculated using the Centers for Disease Control and Prevention’s data file on opioid analgesic morphine milligram equivalents and grouped by tertiles) and initial loneliness score (grouped by tertiles).

Missing data mechanisms will be examined by correlating the proportion of missing data with key baseline characteristics. Multiple imputation by chained equations will be applied to account for loss-to-follow-up. Inferences will be drawn based on two-sided *p*-value of 0.05. Given that all participants are randomly assigned to one of the three intervention arms, we do not expect substantial bias in unadjusted analysis results. Hence, we do not plan to include control variables in our statistical modelling.

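### The plan hypothesises noninferiority between CBT and social prescribing, but gives no margin, direction or active-arm contrast, and is sized only for a 6-point superiority difference

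*Protocol article*

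**What the plan says.** The Hypothesis section of the protocol article expects both active arms to be superior to usual care. It then adds a separate claim about the two active arms: "We hypothesize that CBT and social prescribing will be noninferior". No margin, reference arm, endpoint or time point is attached to that claim there or elsewhere in the article.

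The aim at the end of the Background is framed against usual care: the two interventions are assessed "relative to usual care in reducing loneliness (primary outcome) and opioid misuse (secondary outcome").

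The Power analysis describes one calculation, "allowing us to detect 6-point changes or more in the UCLA loneliness scale (Version 3"). The target comes from published evidence: "The 6-point change was determined by the mean loneliness score change from a previously published meta-analyses of psychological interventions for loneliness". The other inputs are given as "we also assumed a significance level of 0.05, a desired power of 0.80, and a standard deviation of 8.0", and the result is "Based on this, we will require 28 patients per arm", raised to 34 per arm (102 in total) for 80% retention.

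The Quantitative analysis section specifies a linear mixed model: "we will include the intervention arm (control arm as the reference), an indicator for the post-treatment time points", plus their interaction. The one further contrast it announces compares the second and third time points, not the two active arms. The decision rule is "Inferences will be drawn based on two-sided" p-values of 0.05.

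**The concern.** A noninferiority claim needs a margin, a direction, and a confidence limit set against that margin. The margin also determines the sample size. Here the hypothesis is about noninferiority, while the sample size and the inference rule are about superiority. The three parts do not match.

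The comparison matters to readers. The article's title names the two active interventions, and they need different staff: a behavioral health clinician for CBT, and a navigator who may be a peer or community member for social prescribing. A conclusion that one is no worse than the other could influence which a clinic adopts. With a noninferiority hypothesis on paper and a superiority p-value as the only rule, a nonsignificant difference between the arms could be taken as support for the hypothesis, which it would not be.

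**Working it through.** **Inputs from the Power analysis section:** difference 6 points, SD 8.0, alpha 0.05 (two-sided, from the Quantitative analysis section), power 0.80, 28 evaluable per arm. **Assumed, because the article states none:** noninferiority margin M of 2 to 6 points, true difference 0, one-sided alpha 0.025 (the limit of a two-sided 95% interval).

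**1. Reproduce the plan's figure.** n per arm = 2 × SD² × (1.96 + 0.8416)² / difference² = 2 × 64 × 7.849 / 36 = 27.9, so 28. The stated size is an ordinary two-sided superiority calculation for two means.

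**2. Precision of CBT minus social prescribing at one time point.** SE = 8 × √(2/28) = 2.138. The 95% half-width is 1.96 × 2.138 = 4.19 points, about 70% of the 6-point effect (4.19 / 6).

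**3. Noninferiority power and size.** Power at 28 per arm = Φ(M / 2.138 − 1.96). Size for 80% power = 2 × 64 × 7.849 / M².

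| Assumed margin M | Power at 28 per arm | Evaluable per arm for 80% |
|---|---|---|
| 2 | 15% | 252 |
| 3 (half the assumed effect) | 29% | 112 |
| 4 | 46% | 63 |
| 5 | 65% | 41 |
| 6 (the whole assumed effect) | 80% | 28 |

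For example, at M = 3: 3 / 2.138 − 1.96 = −0.557, and Φ(−0.557) = 0.289.

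**4. Allow for the planned repeated measures.** Suppose all pairwise correlations between baseline and the two follow-ups equal ρ (assumed). The change from baseline to the mean of the two follow-ups then has variance SD² × f, with f = (1 + ρ)/2 + 1 − 2ρ. The SE becomes 2.138 × √f, and the margin that gives 80% power becomes 2.8016 × 2.138 × √f = 5.99 × √f.

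| ρ | f | Power at M = 3 | Margin for 80% power |
|---|---|---|---|
| 0.5 | 0.75 | 37% | 5.2 |
| 0.7 | 0.45 | 55% | 4.0 |
| 0.8 | 0.30 | 73% | 3.3 |

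A 3-point margin stays below 80% throughout this range. Correlation within the therapy groups of 6–10 participants would reduce these figures. The article gives no intraclass correlation, so I put no number on that.

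**5. Chance of a nonsignificant two-sided test when one active arm is truly worse** (28 per arm, one time point): 71% if 3 points worse, 54% if 4 points worse, 20% if 6 points worse.

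**The case against.** The strongest reply is that the trial's stated purpose is comparison with usual care. The abstract and the aim say so, the sample size and the reference coding match it, and noninferiority takes up one sentence that no later section turns into an objective or a decision rule. This stands, and it limits the weight of the point.

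Three further objections also stand in part:

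- **The contrast is available.** A reader might infer from the control-arm coding that the model can compare each active arm only with usual care. It cannot be read that way: reference coding labels the parameters, and CBT minus social prescribing is the difference between the two arm-by-post interaction terms of the same fit. A 95% interval from that contrast would also serve a noninferiority test once a margin existed. What is missing is the specification.
- **The margins are not the plan's.** All the power figures for noninferiority depend on assumed margins, and the single-time-point SE ignores the repeated measures. Step 4 of the working gives the range that results.
- **This is an article, and an analysis plan may exist.** Contrasts and interval rules are commonly left to that plan, so their absence alone would be no finding. But the hypothesis and the sample size are both fixed in this article. A margin added later would have to live with 28 evaluable patients per arm.

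**Conclusion.** The point holds as a mismatch between a stated secondary hypothesis and the sample size and inference rule given for the trial. On the plan's own inputs and a single time point, 28 per arm gives 80% noninferiority power only at a margin of about 6 points, which would tolerate loss of the entire assumed benefit. With repeated measures that margin could fall to about 5.2, 4.0 or 3.3 points for assumed correlations of 0.5, 0.7 or 0.8, before any loss from clustering. These figures rest on SD 8, no true difference, one-sided 0.025 and margins that I supplied.

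Two stronger readings are not supported. A reader might infer that the investigators will treat a nonsignificant difference as noninferiority. The article nowhere says so; it only leaves that misreading open. A reader might also infer that a clearly worse arm would very likely escape detection. That is fair for a 3-point deficit (71% nonsignificant) but not for one the size of the plan's target effect (20%).

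The primary comparisons with usual care are untouched. This is a secondary claim that the design is poorly placed to support. It should be corrected, but it does not threaten the main result.

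**What to change.** Replace the noninferiority sentence in the Hypothesis section, and add matching text to the Quantitative analysis section, along these lines: the CBT minus social prescribing difference will be estimated from the same mixed model as an explicit contrast with a 95% confidence interval; it is exploratory; the trial is not sized for noninferiority; and no claim of noninferiority or equivalence will be drawn from a nonsignificant result.

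If the investigators prefer to keep the hypothesis, they should prespecify and justify the margin, the direction, the endpoint, the time point and the confidence-interval rule. They should also state the power that 28 evaluable per arm gives for that margin, with the assumed correlation and any allowance for therapy-group clustering made explicit.

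The first route costs a few sentences and the loss of a secondary claim. The second costs more work and would probably show low power unless the margin is wide or the repeated measures are highly correlated. Neither changes the comparisons with usual care.

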## Methods/design

### Study overview

We will conduct a 3-arm randomized controlled trial comparing two-group based, telehealth interventions for loneliness. Participants with loneliness on long-term opioid therapy will be randomized to one of the following arms: (1) CBT intervention, (2) social prescribing intervention, or (3) usual care. We will collect outcomes on loneliness (primary outcome), current opioid misuse, substance use, social connection, depression, anxiety, and function (secondary outcomes) post-intervention and at 3 months follow-up post-intervention. Figure 1 shows the schedule of enrolment, interventions, and assessments.

**Fig. 1 Fig1:**
[figure not shown]
Schedule of enrollment, interventions, and assessments

### Study framework

Our study framework adapts the National Academies of Science, Engineering and Medicine framework on loneliness and social isolation [33] to understand the relationship between long-term opioid use/chronic pain and misuse/substance use disorder with loneliness as a mediating factor (Fig. 2). Specifically, we propose both chronic pain and long-term opioid use as related but unique risk factors for loneliness that can lead to opioid misuse and poor function followed by substance use disorder and overdose mortality risk. Our framework is supported by multiple studies that report on this cyclical association of chronic pain, long-term opioid use and loneliness [34–37].

**Fig. 2 Fig2:**

Study framework for loneliness and opioid misuse

### Participant eligibility

We will recruit patients who are on long-term opioid therapy (defined as ≥ 3 months receiving prescribed opioids [functional definition is ≥ 3 opioid prescriptions each ≥ 21 days apart]) and who meet the following inclusion criteria: English-speaking, 18 years of age or older and score 6 or greater on the 3-item UCLA-loneliness scale (the scale is scored from 3 to 9). The 3-item scale will be used for eligibility while the 20-item scale will be used for outcomes. We will exclude patients who have active cancer, active psychosis, or moderate/severe cognitive impairment using the mini-MOCA, are on palliative care or live in a controlled setting (i.e., assisted living, nursing home or inpatient treatment facility).

### Setting and participant recruitment

We plan to recruit from primary care clinics from 2 health systems that are part of our practice-based research network, the WWAMI (Washington, Wyoming, Alaska, Montana, and Idaho) region Practice and Research Network. We will use two modalities for patient recruitment: (1) electronic health record (EHR) data extraction and (2) clinician referral. For EHR extraction, participating clinics will provide electronic health record (EHR) data that identify patients who meet the inclusion/exclusion criteria (all identifiable from the EHR except for the loneliness score). If patients have not opted out for research, they will be contacted by phone by the project manager (up to 3 contact attempts per eligible patient). For clinician referral, clinicians at participating clinics will be informed about the study via email and/or during a staff meeting and will have the opportunity to refer any patient who is on long-term opioid therapy to the study. For each patient we reach, we will inform them about the study and, if they are interested in participating, administer the 3-item UCLA loneliness scale over the phone to see if they are eligible (score of 6 or higher on the scale).

### Randomization

Prior to randomization, patients will be administered a baseline survey that includes a psychosis and cognitive screener, and demographic questions. After verification of eligibility, patients will be randomized using computer-generated random numbers to one of three groups: (1) CBT, (2) social prescribing or (3) usual care. There will be no stratification. The randomization will be blinded to the members of the study team responsible for data collection.

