### Study intervention platform

Each active intervention (CBT and social prescribing) will consist of eight one hour, weekly group based sessions delivered via telehealth. Each group will consist of 6–10 participants using a HIPAA-compliant zoom platform allowing group members to see and hear each other.

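### Balance between arms across the two health systems is left to chance in both design and analysis; a stratified blocked list and a system-by-post term would secure it at almost no cost.

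*Protocol article*

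**What the plan says.** Setting and participant recruitment: "We plan to recruit from primary care clinics from 2 health systems".

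Randomization: "patients will be randomized using computer-generated random numbers to one of three groups", followed by "There will be no stratification". Whether the list is blocked is neither stated nor excluded. The Power analysis section plans 34 patients per arm, 102 in all, so the target ratio is 1:1:1.

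Study intervention platform: "Each group will consist of" 6 to 10 participants. This applies to the two active arms only.

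Quantitative analysis: the linear mixed model has arm, "an indicator for the post-treatment time points (immediately following the intervention and 3 months after) as well as their interaction as independent variables", and a random intercept per participant. The section argues that random assignment makes substantial bias unlikely, and concludes: "Hence, we do not plan to include control variables in our statistical modelling".

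**The concern.** Health system is the one structural feature of recruitment that is known in advance. Two systems may differ in patient mix, opioid prescribing practice and local social resources. The usual precaution is to balance on such a factor in the allocation list, adjust for it in the model, or both. This plan states that it will do neither, so a fuller protocol or analysis plan could not add either one without contradicting the article.

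The reason given for omitting covariates concerns bias. Randomisation does remove bias in expectation. It does not protect precision, and it does not stop the one trial that is run from having a visibly uneven system mix. With about 34 patients per arm, such unevenness is not rare.

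If the list is also unblocked, arm sizes and the filling of the therapy groups are left to chance too, in a sample with no spare patients.

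**Working it through.** **1. The plan's own figure.** Inputs from Power analysis: difference 6, SD 8.0, alpha 0.05 (two-sided, per Quantitative analysis), power 0.80.
- n per arm = 2 × (1.96 + 0.842)² × 8² / 6² = 27.9, so 28. This matches.
- 34 × 0.80 = 27.2 expected evaluable per arm, just under 28.
- At 27.2 per arm, SE = 8 × √(2/27.2) = 2.17, and power = Φ(6/2.17 − 1.96) = 0.790 (normal approximation). This is the reference for perfectly balanced arms.

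**2. Arm sizes, only if the list is unblocked.** Each of 102 patients goes to a given arm with probability 1/3.
- SD = √(102 × 1/3 × 2/3) = √22.67 = 4.8.
- Simulation (400,000 draws): 95% range 25 to 44; chance that at least one arm has 27 or fewer randomised, 25%; median gap between largest and smallest arm, 9.
- Pairwise power at 80% retention: mean 0.782 against 0.790 balanced, a loss of 0.8 points; 95% range 0.716 to 0.836.

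**3. System mix, only if the list is unblocked.** System shares are not given; 50:50 and 70:30 are assumed.
- At 50:50, the SD of the difference in share between two arms of 34 is √(2 × 0.25/34) = 0.121. P(difference of 0.20 or more) = 2 × [1 − Φ(0.20/0.121)] ≈ 10%. Simulation with random arm sizes also gives 10% (95th percentile 24 percentage points).
- At 70:30 it is 8% (95th percentile 22 points).
- Effect on the estimate: a 20-point imbalance times an assumed gap between systems of 2 or 4 points in change shifts the arm contrast by 0.20 × 2 = 0.4 or 0.20 × 4 = 0.8 points, against a target of 6.

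**4. Validity.** With simple randomisation, an assumed 4-point gap between systems and an unadjusted test, simulated type I error is 0.051. The nominal level holds.

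**5. Precision from adjusting.** With a 50:50 split, a gap d between systems in the analysed quantity contributes 0.25d² to a total variance of 64.
- d = 2: residual variance 63, power 0.796.
- d = 4: residual variance 60, power 0.815.
- Without adjustment: 0.790.

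In the planned model, d has to be a gap in change, for the reason in step 6.

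**6. Which model term does the work.** The treatment effect is the arm-by-post interaction. With complete data and a random intercept it is estimated from within-person changes. A covariate that is constant within a person explains only differences in level, so a system main effect does not reach it. Fitting the model to simulated complete data confirmed this: a system main effect left the interaction estimate and its standard error essentially unchanged, while a system-by-post term moved both.

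**7. Permuted blocks within two equal systems (simulated).** Arm sizes stay within 33 to 35 for blocks of 3 and 32 to 36 for blocks of 6. The 95th percentile of the difference in system share is about 3 percentage points. Mean power is 0.79, as for exact balance.

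**8. Group filling, only if the list is unblocked.** In an assumed batch of 24 recruits, at least one active arm falls outside 6 to 10 in 45% of draws. For batches of 18, 27 and 30 the figure is 73%, 57% and 75%. At 24, if an arm of 12 or more may form two groups, failures fall to 37%.

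**The case against.** The strongest reply is that nothing here is wrong. The choice is disclosed, a reason is given, and unadjusted analysis after randomisation is unbiased at any sample size. That stands. A reader might infer from the lack of stratification and covariates that the result could be confounded by health system. The documents do not support this: chance imbalance is already covered by the standard error, and type I error holds.

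A reader might also infer that arm sizes and group filling are certainly left to chance. The article rules out stratification, not blocking; a blocked, unstratified list also uses computer-generated numbers, and a condensed article may leave blocking to the full protocol. Those figures are therefore conditional. The absence of a system factor is not.

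Nor does the model ignore baseline. Each patient's own baseline outcome enters as a repeated measure, so a constant difference in level between systems largely cancels. Only differences in change matter, and the documents give no evidence of any.

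Finally, group filling depends on recruitment pace and on whether telehealth groups pool the two systems, which the article does not say. Batches of 24 are an assumption. Blocking would not guarantee 8:8:8 in each such batch: with blocks of 3 and 6 within two equal systems, the exact split occurs in about 41% of first batches and 21% of later ones, although later batches fall within 6 to 10 about 99% of the time.

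**Conclusion.** The point holds as a modest design improvement. By explicit statement, balance across the two health systems is secured neither in allocation nor in analysis. The consequence is some precision and face validity, not bias and not a loss of type I error control, and it arises only if the systems differ in change over time.

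The size is small. Adjustment would add roughly 0.6 to 2.5 points of power under assumed gaps of 2 to 4 points. An unblocked list, if that is what is used, would cost about 1 point of power on average, with a worse tail. A difference of 20 percentage points or more in system mix between two given arms would then occur in about 10% of trials at an assumed 50:50 split, and 8% at 70:30. The system shares, the gap between systems and the batch size are assumptions; the documents give none of them.

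**What to change.** In Randomization, replace "There will be no stratification" with concealed permuted-block randomisation, varying blocks of 3 and 6, stratified by health system. If the list is already blocked, say so; only the stratification is then new.

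In Quantitative analysis, amend the statement on control variables so that the mixed model includes health system and its interaction with the post-treatment indicator. The interaction is needed because the main effect alone does not touch the arm-by-post contrast.

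The cost is a different computer list and up to two more model terms, with the sample size unchanged at 102. Allocation within a stratum becomes slightly more predictable, which varying block sizes and concealment limit. If recruitment has begun, only the model terms can still change, and they should be fixed before anyone sees outcome data by arm.
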